## Abstract

**Background:**

Childhood obesity has important effects on the onset and development of puberty. Although a number of studies have confirmed the relationship between obesity and precocious puberty, little is known about the pleiotropic genes of obesity and precocious puberty and the interaction between genes and environment. There are four objectives: (1) to analyze the incidence of precocious puberty in the general population in China; (2) to verify the direct effect of obesity on children’s precocious puberty using a variety of methods; (3) to verify the effect of obesity and its risk gene polymorphism on precocious puberty in a prospective cohort study; and (4) to analyze the interaction effect of genes and environment on pubertal development.

**Methods:**

We will conduct a multi-center prospective cohort study in three cities, which are selected in southern, central, and northern China, respectively. Primary schools in these cities will be selected by a stratified cluster random sampling method. Primary school students from grade 1 to grade 3 (6 to 10 years old) will be selected for the cohort with extensive baseline data collection, including assessment of pubertal development, family demographic information, early development, sleep pattern, dietary pattern, and physical activity. Participants will be followed up for at least three years, and long-term follow-up will depend on future funding.

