## Methods

### Study design, setting, and participants

#### Study design and sampling

This study is a prospective multi-center cohort study sponsored by the Shanghai Children’s Medical Center affiliated to the School of Medicine, Shanghai Jiao Tong University and performed in three cities in southern, central, and northern China, namely, Zhongshan, Guangdong Province, Qufu, Shandong Province, and Dalian, Liaoning Province. According to socioeconomic level and geographical distribution, the districts of Zhongshan, Qufu, and Dalian are stratified into urban districts in the central area and suburban districts in suburban areas. Using a stratified cluster random sampling method, districts and schools will be selected according to geographical location and school size by a random number generator. Grade 1, 2, and 3 children (6 to 10 years old) from primary schools will be included in this study. However, participants with overweight or obesity with a history of hormone treatment in the past 6 months as reported by parents in the questionnaire will be excluded.

We will carry out a nested case-control study, which will be nested in this cohort study. Participants in case-control study will be enrolled in four groups: children with normal weight and normal puberty, with normal weight and precocious puberty, with overweight/obesity and normal puberty, and with overweight/obesity and precocious puberty. And they will be measured body composition, collected venous blood, and stool at baseline, and collected urine samples at baseline and follow-up periods.

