#### Study procedure

Participants will accept anthropometric measuring by clinicians from the three collaborating hospitals, including Bo Ai Hospital of Zhongshan, People’s Hospital of Qu Fu, and Da Lian Children’s Hospital. The cohort study was scheduled to begin in October, 2019, and the first and secondary follow-up visits will be conducted one and two years later, respectively. A flowchart of the study design was shown in Fig. 1, and the investigation contents required at baseline, first visit, and second visit were shown in Table 1.

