#### Physical examination

Anthropometric data, including weight (kg), height (cm), and waist circumference (cm), will be measured for each child standing without shoes and lightly clothed using standard techniques by one observer at baseline and the first and second visit. Waist circumference will be measured midway between the lower edge of the rib and the upper edge of the ilium. All of the measurement indexes will be measured twice and averaged. Overweight and obesity are the main predictors of interest and will be defined by BMI value, which is calculated as weight (kg) divided by height squared (m^2^). Participants will be defined as normal weight, overweight, or obese if their BMI index is between 18.5 and 25 kg/m^2^, greater than 25 kg/m^2^, or greater than 30 kg/m^2^, respectively, according to the age- and sex-specific cutoff standard for 2- to 18-year-old children proposed by the International Obesity Task Force (IOTF) [24, 25]. Children with overweight or obesity and some participants with normal weight (matched for sex and age with children with obesity and overweight) will be recruited to analyze their body composition, including height, weight, fat-free mass, body fat mass, body fat rate, body water, muscle mass, basal metabolic rate, total energy consumption, protein, inorganic salt, and impedance.

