#### Sexual development assessment

The primary outcome is the difference in incidence of precocious puberty between normal-weight and obese children.

Secondary sexual characteristics assessment for boys and girls will be conducted by male and female professional pediatric endocrinologists or pediatric care physicians separately in different rooms to protect the children’s privacy. Breast development will be evaluated by visual inspection and palpation. Girls with overweight or obesity will be subjected to breast ultrasound to evaluate their nodules. In boys, testicular volume (TV) will be determined by palpation and an orchidometer. According to Marshall and Tanner [26, 27], breast and pubic hair development are divided into 5 stages (stages I to V). Precocious puberty will be diagnosed according to the Tanner stage: onset of breast development stage II (B_2_) or pubic hair development stage II (PH_2_) or above before 8 years or menarche before 10 years of age in girls, and PH_2_ or testicular enlargement (TV ≥ 4 ml) before 9 years of age in boys [28–30].

The presence of early puberty will be defined as children reaching a certain stage of puberty earlier than the median age of that stage [31]. According to previous studies, the median age of puberty onset (girls: breast or pubic hair development; boys: pubic hair or testicular volume development) of Chinese adolescents will be referenced [32, 33], and the onset of menarche before 12 years of age in girls and of voice breaking before 13 years of age in boys will also be defined as early puberty [34].

We separately evaluated the tanner stage for each breast among obese girls by using portable ultrasound (US), and chose the larger one as evaluation result. Tanner II by US is characterized as the presence of a hyperechoic retro-areolar nodule with a central star-shaped or linear hypoechoic area, this stage is assumed to mark the start of breast development [35].

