### Data analysis

Categorical variables will be reported as the number and percentage and analyzed by a chi-square test to compare the distribution between groups. The *t*-test, analysis of variance, and Wilcoxon rank-sum test will be used to compare the differences in distribution of continuous variables, which will be described by mean ± standard deviation (*SD*) for normal data or median with interquartile range for non-normal data.

Based on the discovered pleiotropic genes and obesity-related risk loci (SNPS), we will examine the distribution of gene polymorphisms (SNPS). For obesity-related SNPs of these genes, Effect size Weighting was carried out according to the method reported by Speliotes EK et al. [40], and then genetic risk scores (GRS) will been calculated using the method established in our previous study [41].That is, the number of effective Allele genes (Allele) was calculated, then the weighted value was multiplied, and finally the combined GRS of SNPs of all candidate genes in this study was accumulated.

The effects of exposure factors on outcomes will be evaluated after adjusting confounding factors using logistic regression or multiple linear regression. To analyze whether there is a linear trend of GRS among four groups: children with normal weight and normal puberty, with normal weight and precocious puberty, with overweight/obesity and normal puberty, and with overweight/obesity and precocious puberty, the Cochran–Mantel–Haenszel Trend Test will be used. After 3 years’ follow-up, a causal relationship model between exposure factors and outcomes will be established by using Mendelian randomization (MR) and Egger’s regression models and assessed by sensitivity analysis. Statistical analyses will be performed by using IBM SPSS, STATA and R statistical packages. and the level of significance will be set at *p* < 0.05.

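### The article promises at least three years of follow-up and sets its causal analysis after three years, but schedules no assessment beyond year two; boys under 7 at entry are then still below the outcome's age limit

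*Protocol article*

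**What the plan says.** Two places in the protocol article rest on three years. The Abstract (Methods) states that "Participants will be followed up for at least three years" and makes only longer follow-up conditional on funding, so three years reads as the committed minimum. Data analysis sets its causal modelling, by Mendelian randomization (MR) and Egger regression, after three years of follow-up.

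Three places describe a two-year schedule. Study procedure says that "the first and secondary follow-up visits will be conducted one and two years later, respectively", and adds that "the investigation contents required at baseline, first visit, and second visit were shown in Table 1". Table 1 has those three columns and no fourth. Physical examination has the body measurements taken "by one observer at baseline and the first and second visit".

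On the outcome, Sexual development assessment says: "The primary outcome is the difference in incidence of precocious puberty between normal-weight and obese children". A girl is a case with B2 or PH2 before 8, or menarche before 10. A boy is a case with PH2 or testicular volume of at least 4 ml before 9. On entry, Study design and sampling says: "Grade 1, 2, and 3 children (6 to 10 years old) from primary schools will be included".

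**The concern.** The two durations cannot both be right, and the schedule contains no examination that would supply the year-3 outcome on which the causal model is said to rest.

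Follow-up length is not a formality here. A child's status is final only once the child has become a case or has been examined past the relevant age limit. Children enter from age 6 and the limits run up to 9 in boys and 10 in girls, so one year more or less decides how many have a final status. Data analysis names logistic or linear regression for effects on outcomes, and neither allows for unequal observation time. If children still below a limit were entered as non-cases, incidence, which is a stated objective as well as the basis of the primary outcome, would come out too low.

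**Working it through.** **Schedule.** Last scheduled assessment = baseline + 2 years. Stated minimum = 3 years. Shortfall = 3 − 2 = 1 year. The stated three years cannot be reproduced from the visits listed.

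**Inputs** (Table 3, Zhongshan and Qufu only):
- girls: 3993, of whom 2365 aged 6 to <8 at baseline
- boys: 4630, of whom 2821 aged 6 to <8 at baseline
- age limits from Sexual development assessment: girls 8 (B2/PH2) and 10 (menarche); boys 9
- assumption, not in the article: the share *w* of the 6 to <8 band that is aged 6 to <7. Uniform ages give *w* = 0.5; the full range 0 to 1 is shown.

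**Rule.** A criterion is closed for a child when age at baseline + follow-up ≥ age limit. Visits are taken to fall exactly on the anniversaries. Children already diagnosed are resolved whatever their age, so the counts below are upper bounds for a given *w*.

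**Boys, limit 9.**
- Two years: open if age at baseline < 9 − 2 = 7. Number = *w* × 2821. At *w* = 0.5: 1410 (1410/4630 = 30%). Range: 0 to 2821 (0 to 61%).
- Three years: open if age at baseline < 9 − 3 = 6. None.

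**Girls, B2/PH2, limit 8.**
- Two years: open if age at baseline < 8 − 2 = 6. None. A third year changes nothing for this criterion.

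**Girls, menarche, limit 10.**
- Two years: open if age at baseline < 10 − 2 = 8. Number = 2365 (2365/3993 = 59%). No assumption on *w* is needed.
- Three years: open if age at baseline < 10 − 3 = 7. Number = *w* × 2365. At *w* = 0.5: about 1183 (1183/3993 = 30%). Range: 0 to 2365 (0 to 59%).

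| Criterion | Open at 2 years | Open at 3 years |
|---|---|---|
| Boys, PH2 or testicular volume before 9 | 30% of boys (0–61%) | 0 |
| Girls, B2/PH2 before 8 | 0 | 0 |
| Girls, menarche before 10 | 59% of girls | 30% of girls (0–59%) |

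**The case against.** The strongest reply is that this is a drafting slip: three years may loosely mean three annual waves (baseline, year one, year two), and MR can use the outcome at whatever assessment comes last, since the genes are measured at baseline. That is plausible, but three annual waves span two years, and both the Abstract and Data analysis speak of three years of follow-up. The passages still need reconciling.

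Four stronger readings are tempting, and the article does not support them.

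- *Nearly half the cohort has an unknown outcome.* Adding the boys and girls at *w* = 0.5 gives (1410 + 2365)/8623 = 43.8%. But the girls' definition is either/or. All girls have passed the B2/PH2 limit by year two. The only girls who could still become cases are those with no B2 or PH2 before 8 who then reach menarche after the last visit and before 10. The 59% is the share for whom one route is open, not the share whose status is in real doubt.
- *Three years would have given complete ascertainment.* It would for boys. For girls the menarche route would remain open for part of the cohort, because that follows from entry at age 6 and not only from the missing year.
- *The plan counts unresolved children as non-cases.* It does not say so. Handling of incompletely observed children may be set out in a full protocol or analysis plan that is not shown, so the bias is conditional.
- *The primary comparison is biased.* The primary outcome is a difference between weight groups, and understated incidence does not by itself show a distorted difference. Boys make up 1200/1879 = 64% of overweight or obese children and 2801/5395 = 52% of normal-weight children, so unresolved boys could fall unevenly. Table 3 does not cross age with weight status, so neither size nor direction can be worked out.

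**Conclusion.** The contradiction is plain in the current text and nothing in the article resolves it: three years in the Abstract and Data analysis, two years in Study procedure, Table 1 and Physical examination. As written, the causal model has no scheduled year-3 outcome.

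The practical consequence is a possible ascertainment gap mainly in boys under 7 at entry: about 30% of boys under the uniform-age assumption, with a range of 0 to 61% that the published age bands cannot narrow. A year-3 examination would remove it. For girls the consequence is limited to the menarche criterion. These shares describe two of the three cities; the Dalian baseline had not begun at the reported status date. Understated incidence follows only if children below the limit are analysed as non-cases.

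This should be corrected. It is an internal inconsistency that reaches the primary outcome, not evidence that the design fails.

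**What to change.** 1. State one follow-up length in the Abstract, Study procedure, Table 1, Physical examination and Data analysis.
2. Tie the MR/Egger analysis to the last scheduled assessment, not to a year count that has no visit.
3. For incidence of precocious puberty, follow each child to the age at the last assessment held and treat a child still below the limit and not yet a case as censored. Alternatively, restrict the logistic regression to children past the limit. That restriction should depend on attained age alone: keeping early cases while dropping event-free children of the same age would overstate incidence.
4. Report the number of children below each limit at their last assessment, by sex and weight group. The study holds individual ages, so the range above can be replaced by a count.

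Cost: if two years is the true schedule, no extra visit is needed; the price is a shorter stated follow-up and a little more analysis. If three years is meant, a third annual assessment has to be added to the schedule, with its fieldwork. According to Study status, only the first-year follow-up in two cities was complete by April 2022, so either correction was still open at that point.

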**Discussion:**

The findings of this multicenter prospective population-based cohort study may expand previous related puberty development research as well as provide important information on the mechanism of early puberty. Targeted interventions can also be developed to improve adolescent health problems related to puberty development based on the available evidence.

**Trial registration:**

ClinicalTrials.gov Identifier: NCT04113070, prospectively registered on October 2, 2019.

## Background

The high prevalence of childhood obesity has become a concerning public health problem. In 2016, over 340 million children and adolescents aged 5–19 globally were overweight or obese [1]. Moreover, an increasing number of countries are seeing earlier onset of puberty in children [2–4]. Early puberty has been reported to have a positive association with psychological symptoms, conduct problems, and reproductive diseases [5, 6]. Puberty is a critical but complex process, since many factors, including genetic [7–9], nutritional [10], and environmental factors [11], may influence its development.

Recently, growing evidence from cross-sectional [12–14], and longitudinal studies [15] has indicated that obesity or a higher body mass index (BMI) is associated with earlier timing of puberty in girls. However, the relationship between obesity and timing of puberty onset in boys is inconsistent. Although several studies reported that boys with higher BMI or obesity are more likely to experience early puberty [12, 15, 16], some studies have suggested that delayed puberty is associated with obesity [17, 18].

The occurrence of precocious puberty is closely related to obesity, and there exists some common pathogenesis. A previous study found a positive correlation between obesity and the level of leptin, a protein secreted by peripheral mature adipocytes; moreover, leptin and its receptor play key roles in the initiation of puberty onset and are important biomarkers involved in the regulation of both obesity and precocious puberty [19]. Genetically speaking, over 600 genetic locus are associated with obesity, and many studies have focused on the *LEPR*, *MC4R,* and *FTO* genes [20, 21]. In addition, precocious puberty is related to the *KISS1*, *MC4R*, and *LEPR* genes [7–9]. Consequently, pleiotropic genes like *LEPR* and *MC4R* could influence the phenotype of both obesity and precocious puberty; however, their effect on precocity puberty and its magnitude are still unknown.

Previous studies on the relationship between obesity and precocious puberty have mostly been cross-sectional studies, with few studies on pleiotropic genes of obesity and puberty. To explore the relationship between obesity and puberty development, this prospective cohort study will investigate the genetic, parental, social and family environment, lifestyle, and other determinants of puberty development. This protocol describes an overview of the design and methods of this cohort study, which is funded by the National Natural Science Foundation of China (grant number 81872637). The study objectives are as follows: I) analyzing the incidence of precocious puberty in the general population in China, examining the direct effect of childhood obesity on precocious puberty; II) exploring the relationship between prepuberty obesity and its risk genes and precocious puberty; III) determining the relationship between prepuberty obesity and its risk genes and hormone levels among children with precocious puberty; and IV) analyzing the interaction effect between genes and environmental factors on precocious puberty.

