#### Sample size

Based on the formula for calculating the sample size of a cohort study at one-side significance level: [22].$$N={\left[\frac{u_{\alpha}\sqrt{2\overline{p}\left(1-\overline{p}\right)+}{u}_{\beta}\sqrt{p_1\left(1-{p}_1\right)+{p}_2\left(1-{p}_2\right)}}{p_1-{p}_2}\right]}^2$$

According to the previous studies, the prevalence of precocious puberty was 4.85% (*P*_2_) and 8.43% (*P*_1_) of children aged 7–10 years with normal weight and overweight, respectively [12, 23]. A type I error (*α*) of 0.05, u_0.05_ = 1.96;, β = 0.10, u_0.10_ = 1.28; and a loss of follow up rate of 15%, a total of 4152 children will be required in each center. Finally, inverse-variance weighting (IVW) methods will be used to adjust the sample size.

Based on the SNP gene differences between different groups reported in the literature, Quanto 1.2.4 software (John Morrison, W. James Gauderman 2009, University of Southern California) was used to estimate sample sizes for each group. According to the previous pre-experimental results of obesity study showed that the allele frequency was 0.30 and the minimum allele frequency (MAF) was 0.10 using Additive Genetic Model (ADD), the type I error (α) of 0.05, the actual Power is 0.80, we need average of 800 participants per group and 3200 cases for four groups. Cases among four groups will be controlled by sex and age.

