## Discussion

In this protocol, we described the study design, data collection methods, and analysis of a prospective cohort study in a population-based primary school children. According to the geographical distribution, we chose three cities in northern, central, and southern China and did our best to carry out this study to ensure the representativeness of the population. Students in grades 1 to 3 in randomly selected primary schools are expected to represent local school-age children.

By collecting information on factors such as children’s family environment, lifestyle, and genes, this study will analyze the effect of these factors on children’s physical development from the perspectives of heredity and environment. As a longitudinal study, this study will start earlier in development than previous studies to capture the impact of early childhood experiences on puberty development. Puberty is defined through visual and palpation inspection by a clinical doctor combined with ultrasonic diagnostics; previous studies have depended on self-reports or clinical palpation by non-professional volunteers, which are less sensitive and precise measurements, especially for breast development assessment among obese girls, which may lead to overestimating the precocious puberty detection rate among obese girls, since it is difficult to distinguish adipose tissue and breast tissue, so we will use ultrasonic examination in this study. Although the relationship between obesity and the sexual development of children has been confirmed in both genders by many earlier studies, due to the racial differences in the influence of obesity on sexual precocity, the relationship between obesity and early development is controversial among boys. Through this prospective cohort study, we will further investigate the relationship between obesity and development among Chinese mainland children.

To expand the previous research on puberty development, this study starts from the gene pleiotropy of obesity and takes the lead in studying the influence of the genetic polymorphism of obesity on precocious puberty. Although studies on genetic polymorphism of obesity or precocious puberty in girls have been performed previously, there has been no report on the combination of the two phenotypes, which is expected to reveal the genetic mechanism of the association between childhood obesity and precocious puberty.

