**Districts**			
Urban	3151 (78.91)	3518 (75.98)	6669 (77.34)
Suburban	842 (21.09)	1112 (24.02)	1954 (22.66)

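### Objective I claims incidence for the general population in China, but the sampling frame is grade 1–3 pupils in urban and suburban districts of three chosen cities

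*Protocol article*

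**What the plan says.** The first objective appears twice with the same target. The abstract gives it as "to analyze the incidence of precocious puberty in the general population in China"; the Background gives it as "analyzing the incidence of precocious puberty in the general population in China, examining the direct effect of childhood obesity on precocious puberty".

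Study design and sampling describes a study "performed in three cities in southern, central, and northern China" and names Zhongshan, Qufu and Dalian. Their districts "are stratified into urban districts in the central area and suburban districts in suburban areas". Districts and schools are then drawn at random by location and school size, and children in grades 1 to 3 (6 to 10 years) are enrolled. The Discussion says that the investigators chose the three cities by geography; no random draw of cities is described.

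Sample size sets the same requirement for every city: "a total of 4152 children will be required in each center. Finally, inverse-variance weighting (IVW) methods will be used to adjust the sample size".

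The Discussion says the authors tried to ensure that the population is represented. It then makes a narrower claim about the schools: "Students in grades 1 to 3 in randomly selected primary schools are expected to represent local school-age children". The limitations listed there concern parent-reported diet and activity, and the number and ethnic basis of the genes and SNPs. They do not mention the restriction to three cities.

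**The concern.** An incidence is a property of a population, so the population named in the objective has to be one that the sample can speak for. Random selection supports inference only to the units from which the draw was made. Here the draw starts below the level of the city. It can support a statement about pupils of the listed districts, but not about children in the rest of China.

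Incidence in China is the first-listed objective and is likely to be quoted. Without a stated limitation, a figure from three cities would be read as a national one. A later analysis plan cannot repair this, because no weighting scheme can represent cities that had no chance of selection.

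**Working it through.** **1. Target against frame**

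| Element | Objective I | Design |
|---|---|---|
| Area | China | Three named cities |
| How cities enter | not addressed | Chosen by the investigators |
| Strata | General population | Urban and suburban districts; no rural stratum named |
| Random selection | not addressed | Districts and schools within the cities |
| Children | General population | Grades 1–3, 6 to 10 years |
| Size | not addressed | 4152 required per city |

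The frame is a small, non-random part of the stated target.

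**2. The plan's figures**

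- Table 3 urban share: 6669/8623 = 77.34%, as printed.
- Planned total: 3 × 4152 = 12,456. The two completed cities total 8623, a mean of 4312, with no split by city. Equal size is therefore a planned requirement and not an observed fact.
- The 4152 is sized to compare 8.43% with 4.85%, not to estimate an incidence. The printed inputs (1.96 and 1.28, equal groups) give 1013.4, so 1014 per group, and 2 × 1014/0.85 = 2386. The figure 4152 appears only with a one-sided test, a continuity correction and four groups: 882/0.85 gives 1038, and 4 × 1038 = 4152. Neither the correction nor the factor four is stated. That is a separate matter and does not decide this point.

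**3. What three cities could say about a nation, if they had been drawn at random**

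With three cities there are 2 degrees of freedom, and t(0.975, 2) = 4.303. The 95% half-width is 4.303 × SD/√3. The between-city SD is not in the article. The assumed values give:

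- SD 0.5 points: 1.2 points
- SD 1 point: 2.5 points
- SD 2 points: 5.0 points

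For comparison, take the planning rates at the Table 3 mix of normal-weight and overweight or obese children (thin children left out): (5395 × 4.85% + 1879 × 8.43%)/7274 = 5.8%. Treating 12,456 children as a simple random sample gives 1.96 × √(0.058 × 0.942/12,456) = 0.4 points. Read nationally, that interval would look far more precise than the design allows. Because the cities were chosen, even the wider intervals have no sampling basis.

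**4. Does a crude pooled rate have a known bias, even for the three cities?**

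Let r be the urban-to-suburban rate ratio and u the true urban share; neither is in the article. The ratio of crude to weighted rate is (0.7734 + 0.2266/r) / (u + (1 − u)/r).

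| r | u | Crude / weighted |
|---|---|---|
| 2 | 0.30 | 0.8867/0.65 = 1.36 |
| 1.25 | 0.50 | 0.9547/0.90 = 1.06 |
| 1 | any | 1.00 |
| any | 0.7734 | 1.00 |
| 0.8 | 0.50 | 1.0567/1.125 = 0.94 |

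The bias can be upward, absent or downward.

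The same holds across cities. With assumed city rates of 3%, 5% and 9%, equal city weights give 17/3 = 5.7%. Assumed child-population shares of (0.4, 0.1, 0.5), (0.3, 0.05, 0.65) and (0.2, 0.2, 0.6) give 6.2%, 7.0% and 7.0%. With the rates reversed to 9%, 5% and 3%, the same shares give 5.6%, 4.9% and 4.6%.

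**5. Inverse-variance weights would not help**

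At equal city sizes and ignoring clustering, the weights are proportional to 1/(p(1 − p)). For 3%, 5% and 9% these are 34.36, 21.05 and 12.21. The combined rate is (34.36 × 3 + 21.05 × 5 + 12.21 × 9)/67.62 = 4.7%, against 5.7% with equal weights. Such weights follow precision and favour the low-rate city; they do not follow the number of children represented.

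**The case against.** The strongest reply is that incidence is not the main purpose. The primary outcome is the difference in incidence between normal-weight and obese children, and the sample size is built on that contrast. It does not need a nationally representative sample. This stands: the point concerns Objective I only.

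Three stronger readings are tempting, and the article does not support them.

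- A reader might infer that the pooled rate estimates no defined population. It does not follow. Within each city the stratified cluster sample has a definite target, grade 1–3 pupils of the sampled strata, and a design-weighted three-city rate would have one too.
- A reader might infer that an unweighted pooled rate will be published and will overstate the truth, by some 6% to 36% if urban rates are higher and the true urban share is 30% to 50%. The article never states that estimator; its line on numbers and percentages is a general one, and weights may be set out in a document not shown. The range also assumes a direction. A rate ratio below 1 reverses it, and an urban share near 77% removes it.
- A reader might infer that the Discussion contradicts the objective by claiming only local representativeness. The local sentence is about schools, and the sentence before it makes a wider claim about the spread of cities. The wider claim is unsupported, but the two sentences work at different levels.

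It is also fair to say that the absence of rural children is partly inference. The article names no rural stratum, but does not say whether outlying schools are excluded or counted as suburban. None of this closes the gap between a national objective and a three-city frame.

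**Conclusion.** The point holds as a mismatch between the stated objective and the sampling frame. The design supports at most inference to grade 1–3 pupils in the urban and suburban districts of Zhongshan, Qufu and Dalian. The abstract and Background claim more than that, and the limitations do not correct it. This conclusion rests on the article's own description of the sampling and on no assumed figure.

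The size of the error against a national rate cannot be bounded from the article, and neither the direction nor the size of any bias in a crude pooled rate can be determined. The calculations above show sensitivity under stated assumptions; they are not estimates. The comparison of obese with normal-weight children is not affected. The point is worth acting on because it changes what the study may conclude under its first objective, and correcting it costs little.

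**What to change.** - **Objective.** In the abstract and the Background, restate Objective I as the incidence of precocious puberty in grade 1–3 pupils of the urban and suburban districts of Zhongshan, Qufu and Dalian.
- **Reporting.** Give incidence by city and by urban or suburban stratum.
- **Limitations.** Add that the three cities were chosen rather than sampled, and that results do not extend to other areas.
- **Combined rate, if one is given.** Define its target population. Weight by the inverse of the selection probabilities across both stages, district and school, or post-stratify to enrolment. Stratum enrolment divided by sampled enrolment is a post-stratification factor; under two-stage selection it is not in general the inverse selection probability. Do not combine by inverse variance.

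The cost is mainly wording. Enrolment counts should be at hand, since school size enters the selection. The Zhongshan and Qufu baseline surveys are complete, so those samples cannot be changed, but the claim can. The downside is a narrower claim and, if weights are used, slightly wider intervals.
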